#### The mobile phone app

The app for the pilot project was produced by collaboration with ScientificMed Tech AB (now part of Cuviva AB) (http://www.scientificmed.com), and for the current project, the app has been modified based on the previous experiences of the users and the researchers. A workshop with the pilot study participants, researchers and the company showed that the participants wanted the app to be more tailored to their needs with a more user-friendly interface. Both the researchers and the users wanted feedback to be relevant and tailored to the users’ progress, thus supporting change and awareness. As with the previous version, the new version of the app includes six domains for registering daily activities, experiences and behaviours (see figure 1 for examples from the app): my goals (goal achievements on three preset goals); physical activity and steps (step counts, 24-hour time use in relation to exercise, moderately intense activities, sleep, sedentary activities and other activities); engaging activities (participating in health-promoting EEAs); tobacco and alcohol use (consumption); stress (perceived time-pressure) and dietary habits (consumption of fruits/vegetables, breakfast, fish and snacks—not included in the figure). Domains are based on modifiable risk factors for stroke, as presented by the American Heart Association,^3^ with the addition of health-promoting EEAs and stress reduction.

**Figure 1 F1:**
[figure not shown]
An example of a checklist that shows the domains that the participants need to register in the app. Published with permission from ScientificMed Tech/Cuviva AB.

Fidelity and adaptations	Interviews with interventionists on delivery of intervention. Log-books from interventionists.	t2
Dose	Log-books from interventionists.	t2

t1=baseline; t2=1 week following intervention ending; t3=12 months follow-up postbaseline.

*Measures collected via an online survey.

COPM, Canadian Occupational Performance Measure; EQ-5D, European Quality of Life 5 Dimensions; PPR, Daily Experiences of Productivity, Pleasure and Resoration Profile.

#### Outcome data

Outcome assessment methods were carefully chosen to assure methods that are valid and reliable and will capture change. The primary outcome measure is risk for stroke, measured by the Swedish version of the Stroke Riskometer^30 31^ and the Stroke Risk Scorecard.
27 28
 Secondary outcomes include participation in health-promoting everyday activities, measured by COPM,^32^ and self-rated health measured using LiSat-11^33^ and EQ-5D.^34^ Other measures are lifestyle habits (measured using the updated Swedish Lifestyle Survey, Levnadsvaneenkäten),^35^ and activity patterns, as measured using the Swedish version of the Daily experiences of Productivity Pleasure and Restoration Profile (PPR).^36 37^ Survey data will be gathered for health literacy of stroke risk,^38^ experiences of time pressure (stress), cost-effectiveness (eg, self-reported sick leave, healthcare utilisation and use of medication), readiness and motivation for change,^39^ current mobile phone use, and mapping out EEAs. Habitual physical activity will be measured using the activPAL micro activity monitor (PAL Technologies, Glasgow, UK).^40^ The activPAL is a small device, which provides information on the position and acceleration of the body. The monitor is attached to the thigh and will be worn for five consecutive days after baseline and at follow-up (11 weeks and 12 months). Outcomes from the monitor are (1) time spent sitting/lying, standing, stepping, (2) numbers of step counts and (3) sit-to-stand transitions.

#### Outcome data: next of kin

We will collect data from next of kins to the participants in the intervention group via an online survey. The survey will include demographic measures of health and questions on their view of the programme and the support they have given their kin during the intervention period.

#### Process data

The process evaluation will illuminate causal mechanisms and help identify factors that are associated with variation in outcomes, such as contextual and external factors.^26^ Process data include both qualitative and quantitative descriptive data, including logbooks from PHC staff (notes taken during delivery of the programme), course evaluations from the web-based staff training and semistructured exit interviews with participants at risk for stroke and their next of kin (see table 2). Fidelity will be evaluated as the extent to which the programme was delivered as expected. The dose will be assessed as the quantity of the implemented intervention. Adaptation, such as changes made to fit different PHC settings, will be collected during interviews with PHC staff. Reach will be assessed regarding how many eligible patients signed up and how many completed the MMD programme. In addition, adverse events will be registered. Context includes external factors that may act as a barrier or facilitator to the implementation itself and to the interventions’ effects. Assessing barriers and facilitators to programme implementation will also involve evaluating programme feasibility; that is, the extent to which stakeholders regard the MMD as satisfactory in terms of content and complexity/difficulty.

Data will be managed using an online software called RedCap (https://www.project-redcap.org/) in combination with a local data management system.

#### Participant timeline

Participant enrolment started in April 2022, and in June 2023, all 104 participants had been included. The last groups’ 12-month follow-up will occur in March 2024 (marking the end of the study). In total, 5 intervention groups, each consisting of 10–12 participants, will receive the prevention programme during the study.

### Data analysis plan

#### Outcomes on effects

The characteristics of all persons at risk for stroke at inclusion, and outcomes at 11 weeks and 12 months after inclusion, will be presented with descriptive statistics. The treatment effects in the RCT study will be analysed on an intention-to-treat basis, with randomised participants retaining their original allocated group, and measured as differences between groups at follow-up and at 12 months considering plausible confounders. Outcome data will be examined for outliers, normality and missing data. Analyses of covariance will be used for continuous outcomes, with baseline values as covariates. Logistic regression analyses will be used for dichotomous outcomes. The level of significance will be set at p≤0.05 and the confidence level at 95%. We will use the Statistical Package for the Social Sciences (SPSS, Version 29) to analyse the data. Analyses will provide results for the relative effectiveness of the intervention programme. The results will be reported in accordance with the Consolidated Standards of Reporting Trials (CONSORT) recommendations for reporting RCTs on non-pharmacological treatments^41^ and the protocol has been reported according to the Standard Protocol Items: Recommendations for Interventional Trials (SPIRIT) reporting guidelines.^42^

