### Sample size and power considerations

The primary outcome is stroke risk, with emphasis on modifiable stroke risk factors. Based on data from a case study,^27^ we calculate a decrease of at least one level of stroke risk (eg, moving from high risk to medium risk in the Stroke Risk Score Card^28^) with an SD of 1.5, the statistical power of 80%, with two-tailed α=0.05. Under these assumptions, the required sample size was 35 in each group (in total n=70). The Stroke Risk Scorecard was developed as an easy-to-use self-assessment tool by the National Stroke Association in the UK.^28^ The tool has been used previously in a few studies to detect risk factors of stroke^27 28^ and in a recently finished pilot study conducted in the research group (publication in manuscript). Since the Stroke Risk Scorecard has not been sufficiently tested psychometrically, power calculations were added for performance in EEAs. Assuming a difference on performance in EEAs of two points (as measured with the Canadian Occupational Performance Measure (COPM)^29^) a power of 0.8 and a two-sided p value of 0.05 a sample size of 40 participants in each group would be sufficient.

To safeguard against drop-outs (a maximum 30% drop-out rate is assumed), a total of 104 participants will be enrolled in the study (52 in each group).

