The possible limitation of the study will be the reliability of self-reported measures, and there is a risk of bias since reporting might not be accurate, therefore, measures such as activPAL, Body Mass Index (BMI) and blood pressure are complementing the assessments. Although we have planned for 5 days of activPAL wear (the recommendation is 7 days), participants will wear these 24/7, and we will monitor data loss. External validity of the outcomes could be flawed, due to a recruitment process mainly benefiting highly motivated persons at risk of stroke and the risk of drop-outs in less-motivated participants. The power calculations are based on a stroke risk score that has to our knowledge not been used for power calculations previously nor in intervention studies. However, this is the score used in our previous pilot study and most relevant to use, since the aim of the study focuses on modifiable risk factors which are covered in the score. In addition, we have added a power calculation on a secondary outcome.

Ethical dilemmas include that controls are not being supported in the same way as the intervention group and that the recruitment methods could be skewed and fail to reach out to vulnerable groups in society (with lower socioeconomic status [SES]) at risk for stroke. The strength of the study lies in the robustness of the RCT design, the process evaluation and the interprofessional collaboration in a clinical PHC context. The data from the process evaluation will increase and ease the possibility of implementation of a prevention programme for NCDs in PHC. The risk of contamination between control and intervention is deemed minimal, as participants are recruited via social media in a large city.

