### Ethics and dissemination

An approval from the Swedish Ethical Review Authority, Sweden has been granted (Ref. numbers. 2015/834-31, 2016/2203–32, 2019/01444 and 2021-05902-02). Data management will be complying with the general data protection regulation (GDPR), and all data will be stored securely to protect the confidentiality. Participation in the study is not expected to lead to health risks or complications, and potential health consequences will be monitored. Participants who experience any health-related problems during the study will be guided to contact their GP. Participants may choose to interrupt their participation in the study at any time. Researchers can also discontinue a participant’s participation based on health issues, or reasons that might jeopardise that person’s safety. Reasons for interruption will be recorded. For a summary of the consent form, see online supplemental file 1.

10.1136/bmjopen-2023-072037.supp1Supplementary data

The findings of the study will be published in peer-reviewed journals, and the results will be disseminated to participants, the public, PHC staff and decision-makers through national and international conferences, as well as study-specific web pages.

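### The per-visit ANCOVA uses only participants seen at that visit; with up to 30% drop-out, one model over both follow-ups and one sensitivity analysis would serve the intention-to-treat aim better

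*Protocol article*

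**What the plan says.** All references are to the protocol article.

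- *Outcomes on effects* sets the principle: "The treatment effects in the RCT study will be analysed on an intention-to-treat basis, with randomised participants retaining their original allocated group". Effects are "measured as differences between groups at follow-up and at 12 months considering plausible confounders".
- The same section names the model: "Analyses of covariance will be used for continuous outcomes, with baseline values as covariates". Dichotomous outcomes get logistic regression.
- Its only statement on missing data is "Outcome data will be examined for outliers, normality and missing data". No step is attached to the result of that examination.
- *Sample size and power considerations* requires 35 per group for the primary outcome and enrols 52 per group, because "a maximum 30% drop-out rate is assumed".
- The *Discussion* lists among its limitations "the risk of drop-outs in less-motivated participants".
- *Ethics and dissemination* adds: "Researchers can also discontinue a participant’s participation based on health issues, or reasons that might jeopardise that person’s safety". Reasons are to be recorded. Whether outcome collection continues afterwards is not stated.
- *Table 2* shows both primary instruments (Stroke Riskometer and Stroke Risk Scorecard) collected by online survey at baseline (t1), one week after the programme ends (t2, 11 weeks) and 12 months after baseline (t3).

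**The concern.** An ordinary ANCOVA of one visit's outcome can include only participants who have that outcome. Someone who answers the 11-week survey and is then lost contributes nothing to the 12-month ANCOVA, although the 11-week value is on file and is likely to predict the missing one.

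The expected losses may not be harmless. The authors foresee them among less motivated participants, and health-based discontinuation may relate to the outcome in a stroke-risk trial. The arms also carry different burdens: six 90-minute sessions and an app on one side, standard care as needed on the other. Different drop-out in the two arms is therefore plausible, although the article does not predict it.

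At stake is whether the reported contrast describes everyone randomised or only those who stayed. The drop-out allowance in the sample size protects power and does nothing about bias.

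**Working it through.** **1. The plan's own figure.** Inputs from *Sample size and power considerations*: difference 1 level, SD 1.5, power 80%, two-sided α 0.05.

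n per arm = 2 × 1.5² × (1.960 + 0.842)² / 1² = 35.3, which rounds up to 36. The stated 35 is within rounding. Then 36 / 0.70 = 51.4, or 52 per arm, the number enrolled. (40 × 1.3, from the COPM calculation, also gives 52; the article does not say which route was used.)

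At the maximum drop-out, 52 × 0.70 = 36.4, so about 36 per arm remain, with power of about 0.80. Power for the primary effect is therefore covered. What remains is bias and the unused 11-week data.

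**2. When is the named ANCOVA biased?** A simulation used 52 per arm, SD 1.5, 4,000 replicates and ANCOVA on observed cases. Assumed, not in the article: a correlation of 0.5 between baseline and outcome, a correlation of 0.4 between outcome and a motivation score that is not in the model, and the same treatment effect for everyone.

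| Drop-out pattern | Estimate when truth is −1 | Type I error |
|---|---|---|
| None | −1.00 | 0.051 |
| 30% random, both arms | −1.00 | 0.052 |
| About 30% motivation-driven, both arms | −1.00 | 0.054 |
| About 30% motivation-driven in intervention, 10% random in control | −1.16 | 0.086 |

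Only the last pattern is biased, by about 0.16 level towards the intervention.

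**3. What does a joint model recover?** A second simulation, again with 52 per arm and assumed correlations, let loss after 11 weeks depend on the 11-week value and differ by arm.

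- The 12-month ANCOVA was biased by about 0.16 level towards the intervention. A joint model of both follow-ups was nearly unbiased (0.005).
- When loss was random, both were unbiased and the joint model was slightly more precise: SD of the estimate 0.281 against 0.294. The variance ratio is (0.281 / 0.294)² = 0.91, about 9% lower.

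**4. If drop-outs respond less than completers.** Steps 2 and 3 concern who is missing. A separate question is whether those who leave gain less. Let completers gain 1 unit, let a fraction d of the intervention arm drop out, and let drop-outs gain e, with e between 0 and 1. The effect in everyone randomised is (1 − d) × 1 + d × e.

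- d = 0.30, e = 0: 0.70
- d = 0.30, e = 0.5: 0.85
- d = 0.30, e = 1: 1.00

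The article gives no value for e, so the range is 0.70 to 1.00 of the completers' effect.

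**The case against.** The strongest objection is that this treats a condensed article's silence as an error. Missing-data handling commonly sits in an analysis plan, and ANCOVA can be combined with multiple imputation. That is right as far as it goes: the article never says complete-case, never says anyone without an outcome is excluded, and the lack of a named imputation method is not the point here. What stands is that the article does fix a model, and the model it fixes makes no use of the 11-week value when analysing 12 months. A better use of data already being collected is available.

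Some stronger readings are tempting but not supported:

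- *That the plan fails to deliver intention-to-treat.* The article explains the term as analysis by allocated arm, and ANCOVA by allocated arm does not contradict that.
- *That researchers may remove people from the analysis.* The discontinuation sentence concerns participation; it does not say data are discarded or that anyone leaves the analysis set.
- *That the effect will be overstated by 43%.* That is 1 / 0.70 − 1, and it needs three things at once: the planning maximum occurs, every intervention drop-out gains exactly nothing, and everyone who leaves the programme also lacks the outcome. The last is doubtful, since a person can stop attending sessions and still answer an online survey.
- *That motivation-related drop-out is itself biasing.* The Discussion raises it as a threat to external validity, motivation is an inclusion criterion in both arms, and step 2 shows no bias when the loss is alike in both arms.

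It is also fair to say that a mixed model is no complete cure. It adds nothing for people with no follow-up at all, and it does not correct loss driven by motivation that no recorded value reflects. That is why the fix includes a sensitivity analysis.

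**Conclusion.** The point holds as a recommendation to improve the stated analysis. Unless missing outcomes are handled elsewhere, the ANCOVA as named covers only participants observed at each visit and leaves known 11-week values out of the 12-month comparison, in a trial that allows for up to 30% drop-out.

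Random loss, or loss alike in both arms with a common effect, does no harm. Outcome-related loss that differs by arm can favour the intervention, by about 0.16 level where one level is the planned effect. That size rests on assumed drop-out rates and correlations that the article does not give, so the direction and mechanism are firmer than the number. The range of 0.70 to 1.00 rests on the 30% planning maximum and on drop-outs gaining between none and all of the completers' benefit. Confidence is medium, because an analysis plan may already address this.

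**What to change.** 1. For continuous outcomes, replace the per-visit ANCOVAs with one mixed model for repeated measures over both follow-ups: baseline, arm, visit, arm-by-visit and baseline-by-visit. Report the 11-week and the 12-month contrasts from it.
2. Add one sensitivity analysis that imputes missing intervention outcomes from the control arm. It addresses what the mixed model cannot: participants with no follow-up and loss driven by unmeasured motivation.
3. State that the t2 and t3 online surveys are still sent to people who stop the programme, unless consent is withdrawn. The discontinuation rule itself stays as it is.

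Whether to model clustering by programme group is a separate issue and is not part of this change.

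The cost is a revised analysis paragraph, one line on follow-up, and slightly more analysis work. SPSS, the named software, fits the mixed model. The model wording can be changed until analysis begins; the survey line helps only for follow-ups still due.

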### Duration and specific content of the intervention programme

The MMD stroke intervention programme is a 10-week group programme consisting of five sessions over the first 5 weeks, followed by a sixth booster session 5 weeks later. During the intervention, participants will work actively on self-chosen goals, EEAs and habits to change behaviour and lifestyle. A mobile phone app will be used by participants throughout the 10 weeks, supporting their awareness of current lifestyle habits and everyday activities. To form new habits, common situations will be used to cue behaviour change, like seeing an elevator and looking for the staircase, prompting health-promoting behaviour and making a conscious decision to walk the stairs.^30^ The continuation of a change process is expected from the participants following the 10-week programme period, and strategies for self-management are anticipated.

Each session (90 min) has a theme and includes some type of activity such as exercise, making a light snack or taking a walk. Group dynamics and personal experience are used to reflect on EEAs in relation to health, doing and future goals. The sessions and content, presented in table 1, are delivered by a trained health professional, for example, an occupational therapist, physiotherapist or dietician. There are sessions weeks 1–5 and week 10. During weeks 6–9, no sessions are held, instead the participants are expected to self-manage these weeks with the support of a mobile phone app.

**Table 1 T1:** Summary of session themes, concepts and activities supporting a change process

Week	Session theme	Profession	Concepts	Activity
1	1: Risk factors for stroke and engaging everyday activities	Occupational therapist	Health literacy concerning stroke risk, engaging activities, change process, expectations	Peer interview on engaging activities. Learn how to register in the app
2	2: Physical activity	Physiotherapist	Physical activity, physical inactivity	Try a physical group exercise class at a gym
3	3: Diet and health	Dietician	Dietary routines and change	Food lab—prepare and test; for example, healthy snacks/sandwiches
4	4: Balanced everyday life	Occupational therapist	Activity balance and stressors	Relaxation—such as medical yoga or meditation
5	5: The meaning of healthy habits, routines and activity patterns	One of the team members	Current and desired routines/habits, activity patterns and resources	Walk-and-talk—for example, in a forest or a historical walk in the city

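### The stated ANCOVA, logistic regression and sample size treat participants as independent although the intervention arm is treated in five interacting groups; if outcomes correlate within those groups, standard errors are too small

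*Protocol article*

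**What the plan says.** **Analysis.** Under Outcomes on effects, the protocol article says: "Analyses of covariance will be used for continuous outcomes, with baseline values as covariates". Dichotomous outcomes go to logistic regression. Between-arm differences are to take account of plausible confounders. No term for programme group, no mixed model and no cluster-robust variance is named.

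**Delivery.** Randomisation is by individual in blocks of four (Participants: recruitment and eligibility criteria). Under Participant timeline: "In total, 5 intervention groups, each consisting of 10–12 participants, will receive the prevention programme during the study". Sharing experience is one of the programme's four strategies (MMD: a stroke prevention programme), and on the sessions the article says: "Group dynamics and personal experience are used to reflect on EEAs in relation to health, doing and future goals". Controls receive ordinary primary care individually (Data collection).

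**Sample size.** Under Sample size and power considerations: "we calculate a decrease of at least one level of stroke risk", "with an SD of 1.5, the statistical power of 80%, with two-tailed α=0.05", giving 35 per arm. For the added COPM calculation, "a sample size of 40 participants in each group would be sufficient". Enrolment is set at 52 per arm because "a maximum 30% drop-out rate is assumed". Neither calculation mentions an ICC or a design effect.

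**The concern.** This is an individually randomised group-treatment trial, partially nested: one arm is clustered after randomisation and the other is not. Participants who share sessions, a delivery team and peers may end up with more similar outcomes than participants in different programme groups. If so, the intervention mean rests partly on five group-level deviations, which average out over five groups and not over 52 people. Ordinary ANCOVA and logistic regression count that variation as independent participant noise. The standard error of the arm difference is then too small, the confidence interval too narrow, and the nominal 5% test rejects too often. The stated sample size would also deliver less power than claimed once the analysis is made valid.

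**Working it through.** **1. Reproduce the plan's figure.** Inputs from Sample size and power considerations: difference 1, SD 1.5, power 80%, two-sided α 0.05.

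n per arm = 2 × [1.5 × (1.960 + 0.842)]² = 35.3, against the stated 35. It reproduces only with a design effect of 1, that is, with independent participants.

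**2. Retention.** 52 × 0.7 = 36.4, so about 36 per arm remain at the assumed maximum loss. Average programme-group size is m = 52/5 = 10.4 with full retention and 36/5 = 7.2 after 30% loss.

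**3. Variance inflation.** With clustering in one arm only, and equal total variance in both arms:

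VIF = {1 + [1 + (m − 1) × ICC]} / 2 = 1 + (m − 1) × ICC / 2

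Type I error of the unclustered test = 2 × [1 − Φ(1.96 / √VIF)]

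The article gives no ICC, so 0 to 0.10 is an assumed range.

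| ICC | VIF, 52 per arm | Type I error | VIF, 36 per arm | Type I error |
|---|---|---|---|---|
| 0 | 1.00 | 5.0% | 1.00 | 5.0% |
| 0.02 | 1.09 | 6.1% | 1.06 | 5.7% |
| 0.05 | 1.24 | 7.8% | 1.16 | 6.8% |
| 0.10 | 1.47 | 10.6% | 1.31 | 8.7% |

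Simulating the baseline-adjusted ANCOVA (20,000 trials per ICC; programme groups of 11, 11, 10, 10, 10 against 52 controls; baseline correlation 0.5) gave 5.0%, 6.2%, 7.7% and 10.2%. With 36 per arm it gave 5.1%, 5.7%, 6.7% and 8.5%.

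These figures define the ICC on the variance left after baseline adjustment. If it is defined on total variance, an ICC of 0.10 becomes 0.10/0.75 = 0.133 after adjustment. VIF is then 1 + 9.4 × 0.133/2 = 1.63 with 52 per arm (type I error 12.4%), or 1 + 6.2 × 0.133/2 = 1.41 with 36 per arm (9.9%). Hence the ranges 10–12% and 9–10%.

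**4. Power for one level, SD 1.5, 36 per arm.** Normal approximation: power = Φ(1 / [SD × √(2 × VIF/36)] − 1.96). If the baseline correlation is 0.5 (an assumption), the adjusted SD is 1.5 × √0.75 = 1.30.

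| ICC | No baseline adjustment | Adjusted, correlation 0.5 |
|---|---|---|
| 0 | 81% | 90% |
| 0.05 | 75% | 86% |
| 0.10 | 70% | 81% |

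Using a t reference instead, the unadjusted figures at ICC 0.05 and 0.10 are 74% and 68%. With all 52 per arm retained, the unadjusted normal figures are 86% and 80%.

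**5. Degrees-of-freedom penalty.** Take a test of five adjusted group means against individual controls, 36 per arm. In SD units the variance is [ICC + (1 − ICC)/7.2]/5 + 1/36.

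- ICC 0.05: 0.0364 + 0.0278 = 0.0642, SE 0.253, non-centrality (1/1.30)/0.253 = 3.04, about 11.7 df, power about 79%.
- ICC 0.10: 0.0450 + 0.0278 = 0.0728, SE 0.270, non-centrality 2.85, about 10 df, power about 73%.

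With the ICC defined on total variance these become about 77% and 69%. In simulation this test kept its type I error at 5–6% across ICC 0 to 0.10.

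**The case against.** **The inflation is not established.** A reader might infer that the trial's type I error does exceed 5%. The article does not support that: it gives no ICC, and at ICC 0 the planned test is valid. Contact is six 90-minute sessions, with self-chosen goals, a personal app and four weeks of self-management, which is compatible with a low ICC. At 0.01–0.02 the excess is about one percentage point or less. This stands, and the conclusion has to be conditional.

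**Shared leader and clinic.** A reader might also infer that each programme group has one constant leader, or that clinic effects drive the problem. Table 1 gives sessions to different professions, so at most a team is shared. Clinic or calendar effects common to both arms would not by themselves inflate the error. Peer and delivery effects confined to the intervention arm would. The article itself relies on group dynamics and expects adaptation to different settings (Process data).

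**The power loss can be overstated.** Setting 75% or 70% against the planned 80% ignores two things: the unclustered figure at 36 per arm is 81%, and baseline adjustment could recover much of the loss. It would also be unfair to pair full-retention type I error with maximum-loss power, so both retention scenarios are shown for the error rate.

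**Five groups estimate a variance poorly.** The ANOVA estimate is zero or negative with probability P(F on 4 and 47 df < (1 − ICC)/(1 + 9.4 × ICC)): about 37% at ICC 0.05 (threshold 0.646) and 24% at 0.10 (threshold 0.464). A mixed model then largely reverts to the ordinary ANCOVA. This stands, and it is why the fix needs a fallback.

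**An unseen SAP may handle this.** It may. But the article fixes a named model that does not match its own design, and adjusting for confounders does not deal with correlated errors.

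**Conclusion.** The mismatch between design and analysis is certain from the text; its numerical effect is not. Within-group correlation is plausible because interaction is part of the programme. If it is present, the planned ANCOVA understates the standard error, by a factor of about 1.11 at ICC 0.05 and 1.21 at ICC 0.10 with full retention (the square roots of 1.24 and 1.47). The excess in type I error is small up to ICC 0.02 and material from about 0.05. The power calculation has almost no slack for clustering if 30% drop out: about 36 remain against 35 required under independence. Adequate power for a valid test then depends on the baseline correlation, which the article does not give. The figures assume equal total variance in both arms, near-equal programme groups and, where stated, a baseline correlation of 0.5.

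**What to change.** In Outcomes on effects:

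- **Continuous outcomes.** Replace ordinary ANCOVA with a baseline-adjusted partially nested model: a random intercept for programme group in the intervention arm only, arm-specific residual variances and Satterthwaite degrees of freedom. SPSS, the planned software, can fit it.
- **Fallback or check.** Pre-specify a Satterthwaite test of baseline-adjusted group means against individual controls, because a zero variance estimate is common with five groups.
- **Dichotomous outcomes.** Present clustered analyses as sensitivity analyses, since five clusters are too few to rely on.
- **Reporting.** Report the estimated ICC. In Sample size and power considerations, restate power as conditional on a stated ICC range such as 0 to 0.10.

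The cost is one variable (programme-group membership, known from delivery) and revised wording. The downside is wider intervals and roughly 10–12 degrees of freedom at ICC 0.05–0.10 after 30% loss. Enrolment is complete and need not change.
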